### Methods in analysis to handle protocol non-adherence and any statistical methods to handle missing data {20c}

Additionally, per-protocol analysis for completers defined as participants who received one or more group sessions and at least one individual session is performed. No further methods will be used to handle missing data.

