### Sample size {14}

In GAIN 1.0, we found a mean difference in the improvement of 7.6 points between EUC + GAIN and EUC on the RPQ 3 months after end of treatment. In GAIN 2.0, we hypothesize a difference in the improvement of 7 points between groups on the RPQ. Using the data from GAIN 1.0, the statistical power of the stepped-wedged design can be estimated. With the assumptions of a population mean RPQ change of 9.3 points of EUC + GAIN compared with EUC, measurement variance of 137, a variance between clusters of 0.97, a statistical significance level of 5%, and a statistical power of 80%, we will need 180 participants, i.e. six participants in each of the six clusters for every of six intervention periods. In the first GAIN study, we recruited 55 citizens each year in the age group between 15 and 30 years. By expanding the range of age and offering the intervention in five clusters covering 17 municipalities, we expect to recruit at least 180 participants in the project period.

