### Plans to promote participant retention and complete follow-up {18b}

Responses to questionnaires will be observed closely, and reminders are managed by the project data manager and a project assistant. In case of no or incomplete response to the questionnaires, participants will be contacted twice by e-mail, and lastly by telephone to collect as a minimum RPQ data by an interview. Non-responders will be included in the analyses of registry-based outcomes (see the “Outcomes {12}” section and Additional file 1).

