## Statistical methods

### Statistical methods for primary and secondary outcomes {20a}

Analyses are handled on an intention-to-treat basis. The primary outcome, RPQ, is analysed by using linear mixed-effects models with fixed effect of intervention arm and time (baseline, end of treatment, and 3 months after end of treatment) in interaction and random effects of clusters and subjects within clusters. Similarly, to evaluate clinical significance, we calculate the relative risk in each intervention arm of having an RPQ total score ≥ 20 at 3 months after end of treatment as well as the number needed to treat for prevention of one additional subject with RPQ total score ≥ 20. The secondary outcomes are analysed using linear mixed models similar to those described for the primary outcome using the secondary outcomes as dependent variables instead of RPQ. DREAM data will be analysed with time-to-event analysis and logistic regression.

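### The completer analysis filters only the GAIN arm, and the RPQ ≥ 20 relative risk and NNT would rest on responders; both can be biased, although the primary mixed-model estimate is not affected by the completer rule

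*Protocol article*

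**What the plan says.** Statistical methods {20a} sets the main analysis on an intention-to-treat basis: a linear mixed model for RPQ at baseline, end of treatment and 3 months later. To judge clinical significance it adds the relative risk of scoring 20 or more at 3 months and "the number needed to treat for prevention of one additional subject with RPQ total score" of 20 or more. It gives no model for these binary figures and no rule for a missing 3-month score.

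Section {20c} covers non-adherence and missing data together. It says that an additional "per-protocol analysis for completers defined as participants who received one or more group sessions and at least one individual session is performed". It then closes the subject: "No further methods will be used to handle missing data".

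Intervention description {11a} presents the sessions as parts of GAIN only: three group sessions and up to five individual ones. No completer criterion is given for EUC.

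Section {18b} plans two e-mails and then a telephone call to obtain at least the RPQ. Of those still missing it says "Non-responders will be included in the analyses of registry-based outcomes"; it offers no self-report analysis that includes them.

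**The concern.** Two explicit choices cause the difficulty; neither is a detail left to an analysis plan.

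First, the completer rule cannot be met in EUC. Read literally, no EUC participant qualifies. Read practically, GAIN is filtered and EUC is not. Either way the contrast is no longer between groups formed by randomisation. Selection is plausible because GAIN participants may wait up to 3 months to start and have homework between sessions. Those who never start may be sicker or may already have recovered, so the sign of any bias is unknown.

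Second, a mixed model fitted by likelihood uses everyone with at least one RPQ score, but a risk calculated at a single visit does not. With further methods ruled out, a participant without a 3-month RPQ drops out of the relative risk and NNT, despite the intention-to-treat statement. Response could differ by arm: Outcomes {12} schedules four extra RPQ, BRIQ and B-IPQ measurements during the intervention in EUC + GAIN only, which could raise engagement or cause survey fatigue.

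At stake are the supporting per-protocol result and the figures meant to convey clinical significance.

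**Working it through.** **1. The plan's own figure.** Inputs from Sample size {14}: "we hypothesize a difference in the improvement of 7 points between groups on the RPQ"; "measurement variance of 137, a variance between clusters of 0.97"; "a statistical significance level of 5%, and a statistical power of 80"%. From the Fig. 1 caption: five clusters, six periods, a mean of six participants per box. Total: 5 × 6 × 6 = 180. I take the test as two-sided, since the section does not say.

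Hussey–Hughes variance (random cluster effect, fixed period effects), with s² = 137/6 = 22.83, τ² = 0.97, I = 5, T = 6, U = 15, W = V = 55:

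Var = I·s²(s² + Tτ²) / [(IU − W)s² + (U² + ITU − TW − IV)τ²]
= 5 × 22.83 × 28.65 / (20 × 22.83 + 70 × 0.97) = 3271 / 524.6 = 6.236, so SE = 2.497.

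Power at 7 points: Φ(7/2.497 − 1.960) = Φ(0.843) = 80.0%. The 180 reproduces. The same section also mentions "a population mean RPQ change of 9.3 points of EUC + GAIN compared with EUC"; that gives Φ(1.764) = 96.1%, so 9.3 is not the difference behind 180. I use 7 points as the yardstick.

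**2. The completer filter.** GAIN occupies 5 + 4 + 3 + 2 + 1 = 15 of the 30 boxes, so each arm has about 90 participants. Suppose GAIN has no effect, RPQ change has SD √137 = 11.7, and it correlates ρ with a latent adherence score whose lowest fraction q fails the rule. Removing them from GAIN alone shifts the contrast by

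bias = ρ × 11.7 × φ(z_q)/(1 − q).

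Example, q = 10%: φ(−1.282)/0.9 = 0.195; 0.195 × 11.7 = 2.28; so 0.23 at ρ = 0.1 and 0.68 at ρ = 0.3.

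| q (assumed) | GAIN participants removed, of 90 | Bias, ρ = 0.1 | Bias, ρ = 0.3 | Share of 7 points |
|---|---|---|---|---|
| 5% | 4.5 | 0.13 | 0.38 | 2–5% |
| 10% | 9 | 0.23 | 0.68 | 3–10% |
| 20% | 18 | 0.41 | 1.23 | 6–18% |
| 30% | 27 | 0.58 | 1.74 | 8–25% |

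At ρ = 0 the bias is zero. A negative ρ (non-starters already recovered) gives the same size with the opposite sign. The documents state neither q nor ρ.

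**3. Responder-only relative risk and NNT.** Assumptions: 3-month RPQ is normal with mean 26 in EUC and 19 in GAIN, SD 11.7. The risks of a score of 20 or more are then Φ(6/11.7) = 0.696 and Φ(−1/11.7) = 0.466, so the true relative risk is 0.67 and the NNT is 1/0.230 = 4.35. Missingness depends on an observed covariate correlated 0.5 with the outcome. Large-sample simulation (2 million per arm) of the responder-only figures:

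| Who is lost | Missing, GAIN / EUC | RR | NNT |
|---|---|---|---|
| At random in both arms | 15% / 15% | 0.67 | 4.35 |
| Sicker in both arms | 19% / 19% | 0.65 | 4.23 |
| Sicker in GAIN only | 19% / 15% | 0.62 | 3.81 |
| Sicker in GAIN only, heavier loss | 29% / 10% | 0.60 | 3.58 |
| Sicker in EUC only | 15% / 19% | 0.70 | 4.94 |

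Because missingness here depends only on an observed covariate, imputation using that covariate would remove the bias.

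**4. Why a delta adjustment is also needed.** Suppose instead that 25% of EUC and 10% of GAIN do not respond, and that in both arms the risk is 45% in responders and 70% in non-responders for reasons not observed. True risks: EUC 0.75 × 0.45 + 0.25 × 0.70 = 0.5125; GAIN 0.90 × 0.45 + 0.10 × 0.70 = 0.475. True RR = 0.475/0.5125 = 0.93; the risk difference is 0.0375. Responders alone show RR 1.00 and no finite NNT. Imputation under missing at random would not correct this. These rates too are assumptions.

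**The case against.** Much can be said for the plan, and it limits the point.

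- A reader might infer from {20c} that missing data get no method at all. The text excludes *further* methods only, and the mixed model in {20a} already copes with data missing at random. The two sentences of {20c} may also simply answer the two halves of its title in order, so the protocol need not be offering the completer analysis as its missing-data method.
- A reader might infer that poor attenders are dropped. One of three group sessions plus one of up to five individual sessions is enough to count as a completer. Most poor attenders stay in, and the lower rows of the filter table may never be reached.
- The telephone call in {18b} targets exactly the score behind the relative risk and NNT, and it is stated without distinction by arm. Heavily unequal loss must be judged against that safeguard.
- Contact with GAIN therapists is a weak reason to expect unequal response at this visit: the programme ends 3 months earlier, and reminders come from the data manager and a project assistant.
- The word linking the binary analysis to the primary model in {20a} could hint at a model-based risk, but none is specified.
- The completer analysis is additional. An instrumental-variable estimate with five clusters has small-sample problems of its own, so it is not an obvious replacement.

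All of this narrows the scope. It does not supply an EUC counterpart to the completer rule, nor a way for participants without a 3-month RPQ to enter the relative risk and NNT.

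**Conclusion.** The point holds in a limited form. The completer contrast is not a randomised comparison and can be biased: zero if adherence is unrelated to outcome, and about 0.1 to 1.7 RPQ points (2 to 25% of the planned 7) with 5 to 30% non-completion and ρ of 0.1 to 0.3. The RPQ ≥ 20 relative risk and NNT, as written, rest on responders and can move either way; in the simulated cases an NNT of 4.35 became 3.58 to 4.94.

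Every rate and correlation behind these ranges is assumed, because the documents give none. They show what could happen and do not forecast it. It would be tempting to conclude that the trial's main result is biased. The documents do not support that: the intention-to-treat estimate does not use the completer rule, and the mixed model is valid under missing at random. What the primary outcome lacks is a check on departures from that assumption. This should be corrected before analysis, but it does not threaten the design.

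**What to change.** 1. Derive the RPQ ≥ 20 risks, relative risk and NNT after multiple imputation of the 3-month RPQ, done separately by arm. Use baseline and end-of-treatment RPQ, the covariates in {20b} (age, sex, previous mental health issues, recruitment route), cluster and calendar period. The time factor in the {20a} model is measurement occasion, so calendar period must be added explicitly.
2. Add a delta-adjusted sensitivity analysis, with the shift allowed to differ by arm, for both the relative risk/NNT and the primary outcome. Amend the closing sentence of {20c} to match.
3. Keep the completer analysis, but label it exploratory and non-randomised, and state that EUC is unfiltered.
4. Supplement it with a complier-average estimate, with receipt defined as any GAIN session. A two-session definition would treat someone who may have benefited from one session as unexposed. State the exclusion restriction, namely that allocation acts only through sessions received; this needs care because the Discussion expects expectation bias in both arms. Use small-sample inference suited to five clusters.

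The cost is analysis work only, with no change to data collection. The complier-average interval is wider: roughly 1/0.9 = 1.11 times the intention-to-treat width if 10% receive no session, and 1/0.7 = 1.43 times if 30% do, before any small-sample correction.

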### Plans to give access to the full protocol, participant level-data and statistical code {31c}

The data utilised in the current study is defined as sensitive personal data. The data cannot be shared publicly due to existing data protection laws in Denmark imposed by the Danish Data Protection Agency. The access may be granted on anonymised data and case-by-case basis by approval from the project group who has the legal responsibility as owner and data manager. Access will be granted to the extent permissible by the General Data Protection Regulation and the Danish Data Protection Act. In this case, the principal investigator ([name], e-mail: [contact]) will make data available for the investigator through his affiliated research institution in Denmark with approved authority to access the data. The General Data Protection Regulation and the Danish Data Protection Act and regulations prohibit all other forms of data sharing.

### Composition of the data monitoring committee, its role and reporting structure {21a}

Data monitoring committee is not included in the trial as sponsors are not involved in the study design, data collection or analysis and data are collected using public administered systems (REDCap and Statistics Denmark).

### Adverse event reporting and harms {22}

Potential adverse events may actively be addressed through the survey after end of treatment and at 3 months end of treatment or passively through the intervention period if experienced by the therapists. Adverse events during the intervention are additionally registered by the municipal therapists.

### Frequency and plans for auditing trial conduct {23}

Digital voice recordings are performed in group sessions and individual sessions throughout the trial to assess fidelity and adherence to the study protocol after obtaining participants’ written consent for the recordings. After completion of the trial, 10% of the recordings are randomly selected from the group sessions and the individual sessions and checked by independent assessors with regard to adherence to the GAIN protocol. Furthermore, adherence to the treatment manual is monitored by the two neuropsychologists who provide weekly supervision to therapists delivering GAIN through out the study.

### Plans for communicating important protocol amendments to relevant parties (e.g. trial participants, ethical committees) {25}

Any amendments to the protocol having a possible impact on outcome are registered to relevant registries or regulators, i.e. clinical trials, ethics committee in the Central Denmark Region, and record of processing activities including the General Data Protection Regulation. For details on the approved main protocol for the ethics committee; see Additional files 3 and 4.

### Dissemination plans {31a}

The scientific dissemination will be performed by publishing results in international peer-reviewed scientific journals. The intention is to publish positive as well as negative or inconclusive results that will add to the scientific knowledge concerning the treatment of people with persistent PCS. Furthermore, results will be presented at national and international conferences. By the end of the study period, we will host a final seminar to enable the transfer of knowledge to municipalities nationally and patient organisations. In collaboration with the press offices at HNC and in the municipalities, we plan to execute a media strategy, including dissemination of results through social media, webpages, press releases, and feature articles. Furthermore, we aim at publishing popular featured articles in relevant Danish professional magazines. The aim is to inform the public, including people having had a concussion and relatives, health care professionals (e.g. therapists, medical doctors and other medical or social welfare staff), and to reach out for the policy makers outside the participating region and municipalities. In all parts of communication, dissemination and outreach, “Sygeforsikringen danmark” will be acknowledged and mentioned as a funder of the trial.

## Discussion

At present, a limited number of people with persistent PCS in Denmark are offered treatment and the available interventions are very heterogenic. There is an increased consensus that persistent PCS is best understood in terms of a multifactorial bio-psycho-social model [7] but standardised interdisciplinary interventions are lacking. The present study tests the effectiveness of the originally hospital-based GAIN intervention developed by Thastum et al. [15] in a municipality setting. The study involves a realistic and pragmatic setup of the intervention close to participants’ homes.

The present study has some limitations. First, blinding of the clinicians providing the intervention is not possible. This is a general and well-known problem in trials of behavioural interventions. Another challenge is to ensure fidelity to the treatment manual in a new and larger group of therapists. To ensure fidelity, an educational programme in GAIN to train new therapists was developed and piloted in a municipality outside the Central Denmark Region before the study commenced. Furthermore, two neuropsychologists with special knowledge of concussion and persistent PCS, cognitive behavioural therapy, and graded return to activities, are in charge of all group sessions and provide weekly supervision to therapists throughout the intervention period to ensure quality and fidelity. One of the neuropsychologists ([name]) was directly involved in the development of GAIN and was part of the interdisciplinary intervention team in GAIN 1.0. Another limitation is, that the five clusters (consisting of the 17 municipalities) participating in the trial have different approaches to usual care for people with persistent PCS, and some municipalities may offer more to participants allocated to EUC than others. This may reduce the estimated treatment effect of GAIN. Further selection bias may be an issue if proper randomisation of the five health clusters is not achieved. This will however be accounted for in the data analysis. Expectation bias may also affect both the intervention group and the control group in respectively positive and negative directions. The clinical assessment and advice at baseline may however partly adjust for the negative effect in the control group.

Finally, as the group sessions are a vital part in the GAIN programme, it is necessary to accept a recruitment period of 3 months to be able to include a group of four to nine persons in each intervention group resulting in a waiting period of up to 3 months before beginning the intervention in the EUC + GAIN group. Therefore, participants in the EUC-only group may on average receive usual care earlier after injury than the EUC + GAIN group receive the GAIN intervention which could reduce the estimated effect of the GAIN programme.

In contrast to the hospital-based intervention in GAIN 1.0, a strength of GAIN 2.0 is that the intervention is delivered in a municipality setting close to the home of possible participants, and it is delivered by therapists employed in the municipalities where this population is normally treated. The municipalities may be a more feasible intervention setting in the future, demanding less transportation for participants and enabling a closer collaboration between therapists and social services in the municipalities.

Furthermore, in GAIN 2.0, the upper limit of 60 years is broader than the upper limit of 30 years of age applied in GAIN 1.0, and the result may therefore be more generalizable.

Another strength is the use of reliable and valid outcome measures based on self-reported surveys not administered by persons involved in the intervention. Moreover, predefined outcomes and trial registration before the beginning of the trial minimise the risk of bias.

A final strength may be the holistic and empowering nature of the GAIN programme in contrast to single symptom or passive treatment strategies.

In conclusion, this trial will provide important information on the interdisciplinary developed GAIN programme and its effectiveness in a municipality setting. If the programme is successful, it will improve and guide future directions for early treatment of people with persistent PCS facilitate wider uptake of GAIN, and thereby reduce personal and economic consequences of concussion.

## Trial status

This is the first version of the protocol dated 30.04.2022. Enrolment of participants began in May 2021 and recruitment will end by November 2022.

## Data Availability

The data in the current study is defined as sensitive personal data. The data cannot be shared publicly due to existing data protection laws in Denmark imposed by the Danish Data Protection Agency. The access may be granted on anonymised data and a case-by-case basis by approval from the project group (PIs and research group). See {31C} for details.

## Abbreviations

PCS: Post-concussion symptoms
GAIN: Get going After concussIoN
GET: Graded exercise therapy
CBT: Cognitive behavioural therapy
EUC: Enhanced Usual Care
EUC + GAIN: Enhanced Usual Care plus GAIN
GP: General practitioners
IADL: Instrumental activities of daily living
USER-P: Utrecht Scale for Evaluation of Rehabilitation-Participation
HNC: Hammel Neurorehabilitation Centre and University Research Clinic
RPQ: Rivermead Post-Concussion Symptoms Questionnaire
BIPQ: Brief Illness Perception Questionnaire
BRIQ: Behavioural Response to Illness Questionnaire
